#### **6.3.1.4 Visit 4 / Day -38**

Visit 4 is optional and will be performed 5 days after Visit 3. The purpose of this visit again is to promote compliance with the swabbing component of the protocol. This visit could be performed onsite or via telephone. If there are any doubts about the quality of the swabbing or compliance, the subject will be re-educated via an unscheduled clinic visit. Sites are to be encouraged to keep in contact with their subjects during each swabbing period.

Adverse event and concurrent medication questioning will also take place at this visit (see Section 7 and 8)

### **6.3.2 Study Period 1 (Treatment period)**

#### **6.3.2.1 Visit 5/Day 0/Baseline**

On Day 0 prior to vaccine administration, the following assessments will be performed and documented:

- Review of Inclusion/exclusion criteria paying particular attention to compliance with the Run-in swabbing requirements and whether HSV-1 was identified by PCR during the Run-in shedding assessment (see Section 5.2 and 5.3);
- Urine samples for urinalysis and pregnancy testing (see Section 6.4.5 and 6.4.6);
- A symptom directed physical examination (see Section 6.4.2);
- Vital signs(see Section 6.4.3);
- Concurrent medication assessment (see Section 7);
- Adverse event questioning (see Section 8);
- Blood samples for:
  - Haematology (see Section 6.4.5);
  - Clinical chemistry (see Section 6.4.5);
- Blood samples for immunological assessments including:
  - ELIspot (T cell responses specific for HSV-2 gD2) (see Section 6.4.5);
  - ELISA (anti HSV-2 gD2 antibodies) (see Section 6.4.5);
  - Exploratory Immune assays (see Section 6.4.5); and
- Review of HSV-2 Symptoms and Swabbing Diary (see Section 6.4.10).

Once the above assessments have been performed, the patient will be randomised. The vaccination/placebo will be administered and the resultant bleb will be inspected and measured in mm. The results of the bleb inspection will be recorded in the source documents.

Vital signs will be measured at 30 and 60 minutes following the administration of the investigational vaccine/placebo. Subjects will be observed during this time.

Adverse event and concomitant medication questioning will occur.

The subject will be issued with an Injection Site Reaction Diary and instructed to view their injection site(s) at the same time each day and record their findings every day for 7 days.

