| Study procedures:  | 
Please refer to Table 1.
 
Screening/ Run in:
 
Subjects who provide voluntary written informed consent will be screened for preliminary eligibility. At screening, subjects will also be invited to provide written informed consent for the optional skin biopsy that will be collected at Visit 10.
 
Preliminarily eligible subjects will commence collecting once daily swabs of genital secretions for HSV-2 testing for 45 days from Visit 2. During this and each subsequent swabbing period,
                                                                                                                                                                                                                                                                                                                                                                                  |

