| Sample size determination:             | 
The sample size for this pilot study has been determined based on practical and logistical constraints. The study is not designed to be powered for hypothesis testing or precision with regard to parameter estimation.
 
.
                                                                                                                                                                                                                                                                                                                                                                                                                                                                                                                                                                                                                                                                                                                                                       |
| Statistical analyses:                  | 
An interim analysis of unblinded immunogenicity and efficacy data is planned In summary
 
 
• Immunogenicity data (ELISPOT and ELISA); and
 
• Viral shedding data
 
 
Since the study is a pilot without consideration given to formal hypothesis testing and statistical power, the focus of the statistical analysis will be descriptive. As such, summary descriptive statistics relevant for the various endpoints will be provided for each of the individual treatment groups at the various study time points. In addition, depending on the similarity of the 2 placebo groups, the placebo groups may also be pooled. If inferential statistical tests or models are employed, they will be viewed as exploratory and descriptive in nature.
 
Detailed aspects of the analyses will be described in the Statistical Analysis Plan prior to breaking of the study blind for both the interim and final analyses.
 |

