### 5.2 Inclusion Criteria

The criteria for entry into the study are:

1. Diagnosis of genital HSV-2 infection confirmed by positive HSV-2 serology or if negative a documented positive HSV-2 pathology result, AND positive PCR for HSV-2 during the Baseline Shedding Assessment prior to randomisation
2. A history of recurrent genital HSV-2 for at least 12 months AND a self-reported history of at least 3 and no more than 9 reported lesion occurrences in the 12 months prior to Screening or, if currently on suppressive therapy, in the 12 months prior to initiation of suppressive therapy.
3. Aged 18 to 50 years, inclusive.
4. Male or female. Women of child-bearing potential must be using two effective methods of contraception and agree to continue to do so from Screening, throughout Investigational vaccine/placebo dosing and for 28 days after the last dose of investigational vaccine/placebo.
5. Has voluntarily given written informed consent.

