### 5.3 Exclusion Criteria

1. Birthmarks, tattoos, wounds or other skin conditions on the forearms which could reasonably obscure injection site reactions.
2. Inadequate venous access to allow collection of blood samples.
3. Female subjects who are breastfeeding and those of reproductive potential with a positive urine beta human chorionic gonadotropin ( $\beta$ -HCG) pregnancy test at either Screening or the Baseline Visit (Visit 5).
4. Received immunomodulating agents (including immunosuppressive agents, interferon or other immune or cytokine-based therapies), and/or systemic chemotherapeutic agents within 60 days of Screening or expected to receive these agents during the course of the study. Stable use asthma inhalers and topical corticosteroids are permitted. All medications will be documented and reviewed for acceptance by the Investigator or a medically qualified nominee.
5. Receiving medication known to have anti-HSV-2 activity within 7 days of the Baseline Shedding Assessment.
6. History of or active serious medical or psychiatric illness which, in the opinion of the Investigator, may impair the ability to provide written informed consent and would interfere with treatment, assessment, compliance with the protocol, or subject safety.

7. History of HSV-1 genital infection, ocular HSV infection, HSV-related erythema multiforme, herpes meningitis or encephalitis.
8. HSV-1 positive PCR result during the Baseline Shedding Assessment.
9. Laboratory blood values:
  - a) Haemoglobin <12.0 grams/decilitre (g/dL) for men and <11.0 g/dL for women
  - b) Neutrophil count <1000/mm^3
  - c) Platelet count <80,000/mm^3
  - d) Aspartate aminotransferase (AST) or alanine aminotransferase (ALT) >1.5 times the upper limit of normal (ULN)
  - e) Amylase >1.5 times ULN (unless serum lipase is >1.5 times ULN)
  - f) Subjects with an estimated creatinine clearance of <80 mL/minute (min)
  - g) INR > ULN
  - h) Hepatitis B surface antigen (HBsAg), Hepatitis C Virus (HCV) antibody or HIV antibody positive.
10. Subject has received any vaccine or investigational drug within 30 days prior to Visit 2, or is due to receive subsequent vaccines during the treatment period.
11. Subject has participated in the past in another clinical trial of a vaccination related to infection with HSV (unless it can be verified that the subject received placebo).
12. Any known or suspected allergies to the study drug or its constituents.

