### 6.2 Visit Windows

Every effort should be made to keep to the study schedule. To allow for some flexibility visit windows have been defined and are dependent upon the study stage. The visit windows are as follows:

Table 2– Visit Windows

| Study Period     | Acceptable Window                                          |
|------------------|------------------------------------------------------------|
| Screening/Run-in | ± 3 days                                                   |
| Study Period 1   | ± 3 days except for Visit 5 which has a window of ± 7 days |
| Study Period 2   | ± 3 days                                                   |
| Follow up        | ± 5 days                                                   |

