Study compliance will be emphasized. The Baseline shedding assessment will commence on the day of Visit 2 in the clinic under supervision of site staff. Subjects will be encouraged to take swabs at the same time each day where possible. (See section 6.4.9).

Adverse event and concomitant medication questioning will be performed. Subjects will be provided with a *Concurrent Medication Form* and *Observation Form* so that they can record information about

medications taken and adverse events between visits. These forms will be reviewed at each clinic visit as part of the adverse event and concurrent medication questioning.

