If subjects have previously experienced lesions outside the above mentioned areas, they will be provided with additional swab(s) to enable this region to be swabbed daily providing the lesion is below the waist.

Subjects who do not collect at least 80% of swabs during the Baseline Shedding Assessment (i.e. at least 36 days) will not meet eligibility criteria for the study (see Exclusion criterion 14).

Subjects who test positive for HSV-1 during the Baseline Shedding Assessment will be excluded from this study.

Swabs will be sent directly to the central laboratory each week for analysis. Prior to shipment, the swabs will be kept in the subject's refrigerator in sealed specimen bags.

Should a subject develop an HSV-2 Outbreak during a scheduled 45 day swabbing assessment, the subject should not interrupt this assessment. Additional swabs taken from the lesions will be collected. Please see section 6.4.10.

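### The ±7-day window for Visit 5 conflicts with the 45-day run-in, and nothing makes randomisation wait for the last run-in PCR results

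*Protocol*

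**What the plan says.** Two eligibility criteria rest on run-in PCR. Inclusion criterion 1 (Section 5.2) requires a confirmed diagnosis "AND positive PCR for HSV-2 during the Baseline Shedding Assessment prior to randomisation". Exclusion criterion 8 (Section 5.3) is an "HSV-1 positive PCR result during the Baseline Shedding Assessment". Section 5.1 allows no exemptions. The protocol uses the names run-in and baseline for the same shedding assessment.

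The synopsis sets its length: "Preliminarily eligible subjects will commence collecting once daily swabs of genital secretions for HSV-2 testing for 45 days from Visit 2". Section 6.3.1.2 sets its start: "The Baseline shedding assessment will commence on the day of Visit 2 in the clinic under supervision of site staff". Table 1 puts Visit 2 on Day -45. Section 6.4.9 places this 45-day assessment before the first vaccination and requires swabs on at least 36 days. On shipment it says: "Swabs will be sent directly to the central laboratory each week for analysis".

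For Visit 5 (Day 0), Section 6.2 gives a window of "3 days except for Visit 5 which has a window of ± 7 days", and footnote 15 of Table 1 agrees. Section 6.3.2.1 has the site review eligibility at that visit, "paying particular attention to compliance with the Run-in swabbing requirements and whether HSV-1 was identified by PCR during the Run-in shedding assessment". Randomisation and the first injection follow at the same visit.

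The protocol gives no laboratory turnaround and no minimum interval between the last swab and Visit 5. It does not require that all run-in results be in hand, and it has no rule for a result that arrives after randomisation.

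**The concern.** Exclusion criterion 8 can be confirmed only when every run-in swab has been taken and read, because a single HSV-1 positive anywhere in the 45 days excludes the subject. The Visit 5 window allows the subject to be dosed while swabs are still due. Even on the nominal day, the last weekly batch may still be in the post or the laboratory.

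Two things are at stake. First, a subject may be vaccinated and only later found ineligible; with 40 subjects, and 5 in each placebo sub-group, each such case counts. Second, the exploratory shedding endpoints compare the number of shedding days after vaccination with baseline. If Visit 5 comes early, the baseline period is shorter than the later 45-day periods, or is completed with swabs taken after the first injection.

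**Working it through.** No power calculation bears on this; the synopsis says "The study is not designed to be powered for hypothesis testing or precision with regard to parameter estimation". The check is a calendar count.

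**The protocol's own figure.** 0.80 × 45 = 36 swab days, which agrees with Section 6.4.9.

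**Swabs taken before Visit 5.** The last swab day is the Visit 2 day + 44. Full swab days before Visit 5 = min(45, Visit 5 day − Visit 2 day).

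- Visit 2 on Day -45: last swab on -45 + 44 = Day -1.
- Visit 5 on Day -7: -7 + 45 = 38 swab days, or 38/45 = 84.4%. The 36-day rule is met, with 7 swabs still to come.
- Visit 5 on Day 0: all 45 taken, the last one 1 day old.
- Visit 5 on Day +7: all 45 taken, the last one 8 days old.

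Visit 2 has its own ±3-day window, so the last swab can move to between Day -4 and Day +2. With Visit 2 on Day -42 and Visit 5 on Day -7, there are 35 swab days (77.8%), and the compliance rule would stop that subject. With Visit 2 on Day -48 and Visit 5 on Day -7, there are 41 swab days; the subject passes with 4 swabs untaken.

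**Results read by Visit 5.** Two assumptions are needed. Batches of 7 swabs are posted on Days -39, -32, -25, -18, -11 and -4, with the final 3 on Day -1. Turnaround (posting to reported PCR) is varied because the protocol does not state it. A batch counts as read if posting day + turnaround is no later than Visit 5. Unread results out of 45, with Visit 2 on Day -45:

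| Turnaround | Visit 5 on Day -7 | Day 0 | Day +7 |
|---|---|---|---|
| 1 day | 10 | 0 | 0 |
| 2–3 days | 10 | 3 | 0 |
| 5–8 days | 17 | 10 | 0 |
| 10 days | 17 | 10 | 3 |
| 14 days | 24 | 17 | 10 |

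The Day -7 column includes the 7 swabs not yet taken. On Day 0, 3, 10 and 17 unread results are 6.7%, 22.2% and 37.8% of the 45.

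**Baseline shedding count.** If shedding is constant and the count is not scaled to swab days, 38 days of observation yield 38/45 = 84.4% of the 45-day count, a shortfall of 15.6%. Visit 5 timing is set before allocation, so in expectation this affects change from baseline equally under COR-1 and placebo.

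**The case against.** The strongest reply is that the protocol already gates randomisation. Eligibility is reviewed first, only subjects meeting every criterion are randomised, and no exemptions are allowed. The window also runs forward: a site with results pending can wait until Day +7, when nothing is outstanding if turnaround is 8 days or less. Section 6.4.9 puts the run-in before the first vaccination, so dosing on Day -7 after a Day -45 start would breach that section. The Study Reference Manual, which is not at hand, may deal with laboratory timing. Shedding is exploratory, and a subject found ineligible late can be left out of the Per Protocol set.

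Much of this stands. A reader might infer that subjects will generally be randomised before their last swabs are read, or that the PCR criteria cannot be applied at Visit 5 at all. The documents do not support either reading, because the window allows waiting and no turnaround is given.

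A reader might also infer that low shedders will be wrongly failed, which would tighten the entry filter on baseline shedding. That does not follow. One early HSV-2 positive settles inclusion criterion 1, so only subjects whose sole positives are among the late swabs are exposed. Even they would be failed only if a pending result were treated as negative, and no text says so. Any estimate of how many would need shedding-episode rates that the protocol does not give.

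What the reply does not remove is the contradiction itself: Section 6.2 permits a visit day that Section 6.4.9 rules out, and the 36-day rule does not catch it. The forward half of the window helps only if sites know to wait, and nothing tells them to. Exclusion from the Per Protocol set does not undo a dose already given.

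**Conclusion.** The concern holds as a conflict between the Visit 5 window and the run-in, together with a missing condition on randomisation. The early end of the window needs no turnaround assumption: with Visit 2 on Day -45 and Visit 5 on Day -7, 7 of 45 run-in swabs do not yet exist, exclusion criterion 8 is unverifiable and the compliance rule is still passed. At Day 0 it is probable rather than certain that some results are unread; the number runs from 0 at a one-day turnaround to 17 at 14 days, under the assumed weekly posting. At Day +7 the problem disappears for turnarounds up to 8 days.

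The main consequence is a late HSV-1 positive discovered after dosing. Its frequency cannot be estimated from the protocol. The effect on inclusion criterion 1 is conditional and narrow. The effect on the baseline shedding count is confined to early visits and exploratory endpoints. This should be corrected, but it does not undermine the descriptive safety analysis.

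**What to change.** Reconcile the Visit 5 window (Section 6.2, Table 2, and footnote 15 of Table 1) with the 45-day run-in (synopsis and Section 6.4.9), so that Visit 5 cannot precede completion of the run-in. In Section 6.3.2.1, state that randomisation takes place only after PCR results for all collected run-in swabs have been reported.

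The cost is a somewhat longer gap between the last baseline swab and the first injection, and a need to say what happens to a lost or unreadable sample so that it does not block randomisation indefinitely. The 73-day screening limit in Section 6.3.1.1 should be checked against the change. If screening tests are done within 14 days before Visit 2 (Section 5.5), the earliest is Day -45 - 14 = Day -59, which leaves 73 - 59 = 14 days after Day 0. Table 1, however, allows screening from Day -73, which leaves none: Visit 5 on Day +7 would then be 80 days after screening.

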#### **6.3.2.2 Visit 6 (Week 1) and 8 (Week 5)**

The subject will return to the clinic one week following the investigational vaccine/placebo at Week 1 and 5. The following procedures will be performed:

- Symptom directed physical examination (see Section 6.4.2);
- Review and collection of the Injection Site Reaction Diary (see Section 6.4.11);
- Collection of blood samples for:
  - Haematology (see Section 6.4.5);
  - Clinical chemistry (see Section 6.4.5);
- Blood samples for immunological assessments including:
  - ELISpot (T cell responses specific for HSV-2 gD2) (see Section 6.4.5);
  - Visit 8 only; Exploratory Immune assays (see Section 6.4.5).
- Adverse event, occurrences of HSV-2 outbreaks and concurrent medication questioning (see Section 7 and 8);
- If the subject has evidence of a hypersensitivity type reaction at their injection site(s) photographs will be taken in a standardized manner (see Section 6.4.8)

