|  | 
mucocutaneous genital sites for viral shedding for 45 days at various time points during the study.
 
If the subject develops lesions at any time of the study, they will be instructed to swab the affected area as soon as possible and to report to the clinic within 24 hours (unless this occurs during the weekend. In this instance, as soon as possible). The clinic will conduct a clinical examination and collect swabs to confirm the diagnosis. The subject will continue to collect a swab from the affected area for viral culture each day until the lesion heals.
 
Subjects will be requested to complete a diary during the shedding assessments and for each week following the administration of the investigational vaccine/placebo. There are two diaries that will be used to capture this information including:
 

• Injection Site Reaction Diary, and

• HSV-2 Symptoms and Swabbing Diary.

 
Safety assessments will be performed immediately prior to each injection(s). If the subject experiences any of the following, their injection(s) will be delayed for up to one week:
 

• Temperature of > 38 degrees Celsius;

• Acute intercurrent systemic illness.

 
If the elevated temperature or acute intercurrent systemic illness does not resolve within 7 days, the Investigator or designee will seek advice from the Medical Monitor.
 |

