#### **6.3.2.3 Visit 7 (Week 4) and 9 (Week 8)**

The subject will receive 2 further investigational vaccinations/placebos in 4 weekly intervals at Visit 7 and 9 according to the assigned randomisation schedule. The following procedures will be performed prior to the administration of the investigational vaccination/placebo:

- A symptom directed physical examination (see Section 6.4.2);
- Vital signs(see Section 6.4.3);
- Urine samples for urinalysis and pregnancy testing (see Section 6.4.5 and 6.4.6);
- Blood samples for:
  - Haematology (see Section 6.4.5);
  - Clinical chemistry (see Section 6.4.5);
- Blood samples for immunological assessments including:
  - ELISA (anti HSV-2 gD2 antibodies) (see Section 6.4.5);

The investigational vaccination/placebo will be administered and the resultant bleb will be inspected. The results of the bleb inspection will be recorded in the source documents.

Vital signs will be measured at 30 and 60 minutes following the administration of the investigational vaccine/placebo. Subjects will be observed during this time.

The subject will be issued with an Injection Site Reaction Diary and instructed to view their injection site(s) at the same time each day and record their findings every day for 7 days.

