#### **6.3.2.4 Visit 10 / Week 8 + 48 hours**

Visit 10 is to be scheduled for all subjects 48 hours after receiving their third vaccination at Visit 8. There is a +/- 12 hour window for this visit.

All subjects will have their injection sites assessed by the Investigator or designee. Any reactions will be recorded in the source notes and the corresponding CRF page. All subjects regardless of whether they have had an injection site reaction will have a photograph taken in a standardised manner. Please refer to Section 6.4.8.

A symptom directed physical examination will be performed (see Section 6.4.2).

Skin biopsies will be taken from all subjects who provide consent at their injection sites. Please refer to Section 6.4.11.

Adverse event, occurrences of HSV-2 outbreaks and concurrent medication questioning will occur (see Section 7 and 8).

The Injection Site Reaction Diary will be reviewed and returned to the subject.

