#### 6.4.5 Blood and urine samples for laboratory tests

Blood and urine will be collected at Screening (Visit 1), Baseline (Visit 5), and scheduled clinic Visits 7, 9, 16 and 22. Blood will be collected at scheduled clinic Visits 6, 7, 8, 9, 11, 12, 15, 16, 17, 18 and 22. Samples for laboratory tests should be collected within the visit window. Detailed instructions on the handling and processing of specimens are located in the Study Reference Manual. The following will be collected at the times specified in Section 6.3.

|                                 |                                                                                                                                                                                                                                                                                                                                                                |
|---------------------------------|----------------------------------------------------------------------------------------------------------------------------------------------------------------------------------------------------------------------------------------------------------------------------------------------------------------------------------------------------------------|
| Haematology:             | Haemoglobin, haematocrit, red blood cell (RBC) and RBC morphology, white blood cell and differential white blood cell count, platelet count,                                                                                                                                                                                                            |
| Chemistry:               | Sodium, potassium, chloride, bicarbonate, BUN, creatinine, total protein, albumin, lipase, phosphorus, AST, ALT, GGT, alkaline phosphatase, total bilirubin, glucose, CPK, calcium, uric acid, GFR*                                                                                                                                                     |
| Coagulation:             | Prothrombin time (PT), partial thromboplastin time (PTT), and International Normalized Ratio (INR).                                                                                                                                                                                                                                                     |

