#### **6.4.9 Genital viral shedding assessments**

Subjects will be educated regarding genital swab collection, diary booklet completion and HSV-2 outbreak management. The requirement for compliance in these aspects of the study should be reinforced as often as possible. Additional unscheduled visits may be scheduled for educational purposes should the Investigator or designee judge that this is required.

Daily genital swabs to detect viral shedding will be performed for 45 days commencing as follows:

1. Run-in Shedding Assessment - prior to the first vaccination.
2. Post Vaccination Shedding Assessment - commencing one week following the third investigational vaccine/placebo (Study Period 1); and
3. Post Booster Shedding Assessment - commencing one week after the booster vaccination/placebo (Study Period 2).

Prior to commencing the first assessment period, each subject will be given written gender specific instructions for obtaining genital swabs.

The subject will be instructed to take the swabs at the approximately the same time of the day. Ideally this will be before bathing.

If the subject does not collect a swab at the planned time they will be instructed to obtain a swab as soon as they are able to. (Provided it is on the same day). If this is not until the following day, they will be instructed to document in the diary booklet that a swab wasn't collected, and the reason for not doing so.

Subjects will be given sufficient swabs and courier supplies to enable them to collect the required number of daily swabs. Each subject will receive:

- Swabs,
- Tubes containing the transport medium,
- Spare swabs in case of error,
- Sample biological bags,
- Prepaid/pre-labelled return mail packs,
- Requisition forms;
- Sample labels;
- Torch (for inspection of the genital region);
- Mirror (for inspection of the genital region);
- 'HSV-2 Outbreak' kits for when a subject develops lesions. This kit includes:
  - Swabs;
  - Tubes containing the transport medium,
  - Sample biological bags,
  - Prepaid/pre-labelled return mail packs
  - Requisition Forms; and
  - Sample labels.

Gender specific instructions for obtaining genital swabs will be provided to subjects at Visit 2.

In summary, men will be instructed to obtain the following swabs:

1. Penile skin
2. Perianal and rectal areas.

Women will obtain the following swabs:

1. Vaginal and vulval area;
2. Perianal and rectal areas.

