##### Injection Site Reaction Diary:

---

The aim of this Diary is to collect information about injection site reactions for 7 days following each vaccination. Information that is to be collected includes the presence of:

- Pain/tenderness;
- Swelling/induration;
- Erythema; or
- Other findings.

Subjects will be provided with a ruler to enable the subject to measure and record the size of any injection site reactions that occur in millimetres (mm). Subjects will be instructed to measure the longest diameter of the reaction area. Instructions on the measurement of reactions will be provided to the subjects within their Diary booklet. Injection site reactions will be graded in accordance with the FDA Guidance for Industry document entitled *Toxicity Grading Scale for Healthy Adult and Adolescent Volunteers Enrolled in Preventive Vaccine Clinical Trial* (2007) except for pain and tenderness (see Section 9.2.1).

The Injection Site Reaction Diaries will be issued and collected at the following visits:

- Vaccination 1- Issued at Visit 5, collected at Visit 6;
- Vaccination 2- Issued at Visit 7 and collected at Visit 8;
- Vaccination 3 – Issued at Visit 9, reviewed at Visit 10, and collected at Visit 11; and
- Booster Vaccination/Placebo – Issued at Visit 16 and collected at Visit 17.

When each Diary is returned by the subject, the site staff will check that it is complete and legible while the subject is in the clinic.

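### Post-dose ELISPOT, ELISA and diary visits are due one or four weeks after the dose, but their ±3-day windows are tabulated at nominal study days and are not stated to move when a dose is delayed by the permitted week

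*Protocol*

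**What the plan says.** **Dose-relative timing.** Section 6.3.2.2 says of Visits 6 and 8: "The subject will return to the clinic one week following the investigational vaccine/placebo at Week 1 and 5". Sections 6.3.2.5 and 6.3.3.3 place Visits 11 and 17 one week after dose 3 and after the booster. Sections 6.3.2.6 and 6.3.3.4 place Visits 12 and 18 four weeks after the same doses. ELISPOT is drawn at Visits 8, 11 and 17, and ELISA at Visits 12 and 18. The 7-day reaction diary follows the same pattern, for example "Vaccination 2- Issued at Visit 7 and collected at Visit 8".

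**Study-week timing.** Table 1 puts these visits in columns headed D35, W9, W12, W25 and W28, with a footnote of ±3 days. In Section 6.2, Table 2 gives Study Period 1 a tolerance of ± "3 days except for Visit 5 which has a window of ± 7 days", and Study Period 2 has ±3 days. Section 6.4.5, which covers the immunological samples, adds: "Samples for laboratory tests should be collected within the visit window".

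**Dose delay.** For a temperature above 38 °C or an acute systemic illness, the Synopsis says that "their injection(s) will be delayed for up to one week". Section 8.6 allows the same delay. On the dose interval, Section 6.3.2.3 states: "The subject will receive 2 further investigational vaccinations/placebos in 4 weekly intervals at Visit 7 and 9".

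**Visit 13.** Section 6.3.2.7 sets it 45 days after Visit 10, at the end of the post-vaccination shedding assessment. Section 6.3.2.5 starts that assessment at Visit 11.

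**The concern.** The two timing rules agree while doses are on schedule. After a delayed dose they separate, and neither Section 6.2, the table footnotes, the visit descriptions nor Section 8.6 says which one governs. Visit 10 shows that the protocol can anchor a visit expressly: it is labelled as Week 8 plus 48 hours, has its own ±12-hour window, and is described as "48 hours after receiving their third vaccination". The five visits at issue have no such label.

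Change from Baseline in ELISPOT and ELISA is the secondary endpoint (Section 4.2), and the diary supports the local-reaction part of the primary endpoint. Swabbing is meant to start one week after dose 3 and after the booster (Section 6.4.9), but in practice it starts at Visits 11 and 17. A site that keeps the tabulated window after a delay would therefore sample, collect the diary and start swabbing too soon after the dose. A site that follows the dose would leave the tabulated window and might log a deviation for a correctly timed sample.

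Visit 13 is a separate slip. The interval is counted from the wrong visit.

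**Working it through.** The plan gives no figure to reproduce. The check is day arithmetic.

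**Inputs** (Table 1 and the visit descriptions):
- Nominal dose days: dose 2 D28, dose 3 D56, booster D168.
- Nominal visit days: Visit 8 D35, Visit 11 D63, Visit 12 D84, Visit 17 D175, Visit 18 D196.
- Window: ±3 days.
- Delay *d*: 0 to 7 days, counted from the nominal dose day (my assumption).

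**Exact visit against the tabulated window.** After dose 2 the exact one-week visit is on D(35 + *d*), and the tabulated window is D32 to D38. The visit is outside when 35 + *d* > 38, that is, when *d* ≥ 4. The other four visits have the same structure and the same threshold. Visit 6 is not affected, because dose 1 defines D0.

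**Can one date meet both readings?** Counted from the dose, 7±3 days gives D(32 + *d*) to D(38 + *d*). This overlaps D32 to D38 when 32 + *d* ≤ 38, that is, when *d* ≤ 6. At *d* = 7 the dose-relative window is D39 to D45, with no overlap.

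**Latest in-window ELISPOT**, in days after the dose: 38 − (28 + *d*) = 10 − *d*.

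| Delay (days) | Latest in-window ELISPOT (7 planned) | Exact visit inside tabulated window? | Some date fits both readings? |
|---|---|---|---|
| 3 | 7 | yes | yes |
| 4 | 6 | no | yes |
| 5 | 5 | no | yes |
| 6 | 4 | no | yes |
| 7 | 3 | no | no |

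**ELISA at *d* = 7.** Dose 3 falls on D63 and the Visit 12 window is D81 to D87, so the gap is 81 − 63 = 18 to 87 − 63 = 24 days, against 28 planned. The dose-relative window, 28±3 days, is D88 to D94, with no overlap. For Visit 18 the booster falls on D175 and the window is D193 to D199, again 18 to 24 days.

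**Diary at *d* = 7.** With dose 2 on D35, the seven diary days are D35 to D41 or D36 to D42, depending on whether the dose day counts. At a visit on D38, 3 or 4 of them are still to come.

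**Visit 13.** Visit 10 is on D58, and 58 + 45 = D103. Swabbing from Visit 11 runs from D63 to D107, since 63 + 44 = 107. By D103, 103 − 63 + 1 = 41 of the 45 days are done and 4 remain. D103 lies inside W15±3 (D102 to D108), so the window does not catch the slip. Counted from Visit 11, Visit 13 falls on 63 + 45 = D108, after the last swab and still inside the window.

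**The case against.** The strongest reply is that the conflict depends on where the ±3 days are anchored. Table 2 gives only a tolerance per study period, and the day and week columns of Table 1 can be read as planned times. On that reading the visit text fixes the due date and the tolerance sits around it, so nothing conflicts. To draw an ELISPOT 3 days after a dose, a site would have to disregard the one-week wording, call in a 7-day diary early and start swabbing early. Section 6.2 offers the windows as flexibility, Section 6.3 has deviations reviewed and classified before unblinding, and Section 6.4.2 has injection sites inspected at every visit after Visit 5, so local reactions do not rest on the diary alone.

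Much of this stands. The dose-relative wording shows the intent, and a sensible site will re-anchor. A reader might infer that the protocol instructs sites to sample at the wrong time; it does not. The reply does not remove the ambiguity: the only days printed against the ±3-day footnote are nominal ones, and Section 6.4.5 ties sampling to the window. Nor can the analysis recover a day-7 draw that was never taken.

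The question of later doses is partly answered already. Section 6.8.3 puts the booster at about 6 months from Baseline, so it does not follow a late dose 2 or 3. Whether dose 3 moves with a late dose 2 is less clear, because Sections 6.3.2.3 and 6.8.3 give both a 4-week interval and Week 8. How to settle that is partly a matter of preference.

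On Visit 13, a reader might infer that four swabs are lost. Section 6.4.9 has swabs sent directly to the central laboratory each week, so only the symptom diary would come in early.

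**Conclusion.** The point holds as a minor one. With a delay of 4 to 7 days the exact visit falls outside the tabulated window, and only at a full 7 days can no date meet both readings. The likely cost is a spurious deviation or an occasional mistimed sample in the few subjects whose dose is delayed, in a pilot whose analysis is descriptive (Section 11).

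A reader might go further and conclude that the secondary endpoint is compromised. The protocol does not support that. It gives neither a rate of delayed doses nor the time course of the immune response, so the effect on the results cannot be sized. The day counts assume that the delay runs from the nominal dose day.

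The Visit 13 rule is wrong as written, whatever the dose timing: on nominal days the symptom diary is collected with 4 days outstanding.

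**What to change.** - Add a footnote to Table 1 and Table 2: Visits 8, 11 and 17 fall 7±3 days, and Visits 12 and 18 fall 28±3 days, after the actual date of the preceding dose. ELISPOT samples then lie 4 to 10 days and ELISA samples 25 to 31 days post-dose, whatever the delay.
- Keep the booster at about 6 months from Baseline, as Section 6.8.3 has it.
- Optionally, say whether dose 3 keeps four weeks from the actual dose 2. Keeping the interval is workable: with doses 2 and 3 each a week late, dose 3 falls on D70 and swabbing runs from D77 to D121, before the Week 19 call (D133) and the booster (D168).
- In Section 6.3.2.7, count Visit 13 from Visit 11, as Section 6.3.3.5 counts Visit 19 from Visit 17.

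The cost is two footnotes and one visit number, with no added visits or samples. A few subjects would finish a study period up to a week later (two weeks if doses 2 and 3 are both late). Their gap from dose 3 to booster would shorten from 168 − 56 = 112 days to 168 − 63 = 105, or to 168 − 70 = 98.
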